#### Demographics

Participant age, gender, race, ethnicity, marital status, education level, primary language, and working status/profession will be collected of all participants immediately following completion of the intervention.

#### McAllister affect-based trust

This 5-item scale [58] assesses perceptions of affect-based trust amongst CFT members. Items center on individual’s perceptions that team members can share ideas freely, that team members listen to one another, that team members care for one another, and that team members are invested in working well with one another. Each participant will complete this measure immediately following their completion of the intervention. Participants respond on a scale ranging from 1 = strongly disagree to 7 = strongly agree, and scale scores are computed by calculating the average item response.

#### Parent Participation Engagement Measure (PPEM)

This 5-item measure originally developed for culturally diverse families served in children’s outpatient mental health, was adapted for CWS home visitation services, and assesses active parent participation, engagement, and voice in treatment services [59]. Each participant will complete the PPEM immediately following their completion of the intervention. Participants respond on a 5-point Likert-type scale ranging from 1 = not at all to 5 = very much. Scale scores are computed by calculating the average item response.

#### Psychological safety

Edmondson’s 7-item Psychological Safety Climate Measure [41] evaluates perceptions of the work environment (in this case, the CFT meeting) as being one wherein policies and procedures foster a safe and comfortable space for interpersonal risk. Each participant will complete the Psychological Safety Climate Measure immediately following their completion of the intervention. Participants respond on a scale ranging from 0 = doesn’t apply at all to 4 = entirely applies, and overall scale scores are computed by calculating the average item response.

#### Working Alliance Inventory Short Form (WAI-SR)

The WAI-SR [60] is a 12-item version of the Horvath and Greenberg’s (1989) Working Alliance Inventory. Each item is responded to using a 7-point Likert-type scale. It yields three summed subscale scores, as well as one summed overall scale score. Each of the subscales will measure proposed mechanisms, while the overall scale will measure proposed outcomes. The 4-item Goal subscale will be used to determine team member agreement on goals for CWS child/family case treatment plan (goal specification). The 4-item Task subscale will be used to determine team member agreement on how to achieve goals for CWS child/family case treatment plan (strategy formulation). The 4-item Bond subscale will be used to determine the personal bond between CFT team members (trust). The overall scale score assesses the collaborative relationship between relevant parties and consensus and willingness by all to engage in and do the work that leads to improvement (CFT Fidelity). Each participant will complete the WAI-SR immediately following their completion of the intervention.

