**Outcomes**			
Feasibility of Intervention Measure (FIM)	AAR Team Implementation Strategy Feasibility		✓
Acceptability of Intervention Measure (AIM)	AAR Team Implementation Strategy Acceptability		✓
Intervention Appropriateness Measure (IAM)	AAR Team Implementation Strategy Appropriateness		✓
Working Alliance Inventory-Short Revised (WAI-SR) Overall Score	CFT Clinical Intervention Fidelity Overall collaborative relationship	✓	✓
Parent Participation Engagement Measure (PPEM)	CFT Clinical Intervention Fidelity Collaboration and engagement	✓	✓
Collaboration & Satisfaction About Care Decisions (CSACD)—Satisfaction	CFT Clinical Intervention Outcome Satisfaction with decisions	✓	✓
SD County Behavioral Health Administrative Data	CFT Clinical Intervention Outcome Behavioral Health Service Linkage	✓	✓

Within team environments, shared mental models refer to the degree to which individual team members perceive key concepts (i.e., team, task) in a similar manner. For the CFT services intervention, shared mental models regarding perceptions of member roles, responsibilities, and goals can mediate more effective and efficient treatment planning. Team affect (i.e., trust and psychological safety) may also serve as mechanisms mediating success of the CFT services intervention. Psychological safety, a group-level phenomenon that correlates with team learning behaviors and performance, facilitates team members’ feelings of security [39] and focus on collective goals and problem prevention, rather than on self-protection [40–44]. Similarly, team trust is associated with decreased inefficiencies, greater negotiating effectiveness, and greater team effort, thus mediating overall team effectiveness [45–47]. Given the sensitivity and high stakes associated with CFT meetings (i.e., child placement, reunification), CFT members—particularly children/family—may feel uncomfortable fully participating for fear of negative repercussions. When CFT members experience enhanced shared mental models, psychological safety, and trust, they may be more open and willing to voice their opinions to collaborate on the treatment planning process for the CWS case.

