### Analytic plan

Multilevel modeling with random intercepts and slopes will be used to examine differences in the targeted outcomes between CFT and CFT + AAR conditions, while accounting for the nested data structure. Specifically, this project will test the main effect of the AAR on implementation outcomes and child/family outcomes. Analyses will include the between-CFT meeting factor of condition (CFT vs. CFT + AAR) and within-CFT meeting factor of individual CFT member participant. The cross-level condition by participant interaction effect on the specified outcomes will be of primary interest.

A cross-level prediction model will test the extent to which the condition effect on the CFT outcomes is mediated by its proximal effect on team processes and emergent states. To assess the extent to which team processes are targeted by the AAR intervention, the Goal and Task subscales of the Working Alliance Inventory-Short Revised (WAI-SR) will be used to assess goal specification and strategy formulation, respectively [60, 63]. The Collaboration subscale of the Collaboration & Satisfaction About Care Decisions (CSACD) [57] measure will be used to assess the extent to which the AAR engages the team processes of communication and coordination. Several measures will be used to assess the extent to which emergent states are targeted by the AAR. Specifically, the Bond subscale of the WAI-SR and the McAllister Affect-Based Trust [58] measure will be used to assess trust. Edmondson’s Psychological Safety Climate [41] measure will assess the extent to which the AAR impacts the emergent state of psychological safety. To assess the extent to which the AAR engages the emergent state of shared mental models, a card-sorting task will assess CFT team shared mental models by examining perceptions of member roles, responsibilities, and goals across CFT team members. The concepts contained in the card sort will be representative of specific CFT roles, task responsibilities, and goals. To determine the feasibility, acceptability, and appropriateness of the AAR for CWS CFTs, those in the CFT + AAR condition will complete the Feasibility, Acceptability, and Appropriateness of Intervention Measures, respectively [51].

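### WAI-SR subscales serve as mediators of the WAI-SR overall score, which is their sum, so those three mediation paths are built in by shared items

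*Protocol article*

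**What the plan says.** All references are to the protocol article.

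- **Instrument and scoring** (Measures, Working Alliance Inventory Short Form): "The WAI-SR [60] is a 12-item version of the Horvath and Greenberg’s (1989) Working Alliance Inventory". On scoring: "It yields three summed subscale scores, as well as one summed overall scale score". Goal, Task and Bond are each described as 4-item subscales.
- **Roles** (same section): "Each of the subscales will measure proposed mechanisms, while the overall scale will measure proposed outcomes". Goal stands for goal specification, Task for strategy formulation, Bond for trust, and the overall score for CFT fidelity.
- **Table 1** repeats these roles. The three subscales are listed under Mechanisms. The "Working Alliance Inventory-Short Revised (WAI-SR) Overall Score" is listed under Outcomes, labelled as fidelity.
- **Analytic plan**: a cross-level model is to test how far "the condition effect on the CFT outcomes is mediated by its proximal effect on team processes and emergent states". The section names Goal, Task and Bond among the measures of these processes and states. It does not exclude them when the outcome is the WAI-SR overall score.
- **Timing**: each participant fills in the WAI-SR once per meeting, directly after it, so subscales and overall score come from one set of answers.

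**The concern.** A mediation analysis rests on two links: condition to mediator, and mediator to outcome given condition. The second link carries the claim about mechanism. If the mediator is an arithmetic part of the outcome, that link is present whether or not the mechanism works as the model says.

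The pairs in question are not peripheral. The section on the mechanistic model routes team processes and emergent states to fidelity, and the WAI-SR overall score is one of only two fidelity measures in Table 1. The Power analysis section concedes that an effective sample of 36 may suffice for mediation only if both paths are large. The shared items make one of the two large by construction, so in a small study these pairs are favoured to look positive over pairs that share no items.

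**Working it through.** **Inputs from the protocol article.** WAI-SR: 12 items, three 4-item subscales, summed scores. Mediation tests: effective sample size 36, from 320 observations with ρ = 0.20; α = 0.05.

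**Reproducing the plan's figures.** 4 + 4 + 4 = 12, so no item of the overall score lies outside the subscales, and Overall = Goal + Task + Bond. The effective sample size is 320 / [1 + (40 − 1) × 0.20] = 320 / 8.8 = 36.4, which matches 36 when the cluster term is 40. It serves below only as the sample size that the plan itself gives the mediation tests.

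**All three subscales as mediators.** Regressing the overall score on condition, Goal, Task and Bond returns the identity: each mediator coefficient is 1, the direct effect of condition is 0 and R² = 1. All of the condition effect is then counted as mediated, whatever the intervention does. The simulations gave exactly this in every setting.

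**One subscale as mediator.** Write T = S₁ + (S₂ + S₃), with unit-variance subscales and a common correlation r between them. The documents do not give r, so it is an assumption.

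- Cov(S₁, T) = 1 + 2r and Var(T) = 3 + 6r.
- Slope of T on S₁ = 1 + 2r. The 1 is the subscale predicting itself; only 2r is empirical.
- Corr(S₁, T) = (1 + 2r) / √(3 + 6r) = √((1 + 2r)/3).

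| r (assumed) | Slope | Correlation with total |
|---|---|---|
| 0 | 1.0 | √(1/3) = 0.58 |
| 0.5 | 2.0 | √(2/3) = 0.82 |
| 0.7 | 2.4 | √(2.4/3) = 0.89 |

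If a is the effect of condition on the subscale, the estimated indirect effect is a × (1 + 2r) = a + 2ra. The first term is the condition effect on the subscale, counted again as mediation.

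**How often the mediator-to-outcome path is significant at n = 36** (single-level simulations, 500 or 1,000 runs per setting):

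| Outcome | r = 0 | r = 0.3 | r = 0.6 |
|---|---|---|---|
| Overall score, items shared | 96–98% | at least 99.9% | 100% |
| Sum of the other two subscales, no shared items | 5–7% | 63–66% | over 99% |

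The r = 0 column isolates the problem. With no relation between subscales the path should be found at about the 5% error rate, and it is once the shared items are removed. With them left in, it is nearly always found. At n = 320 it is found in every run.

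**The mediation test as a whole.** Requiring both paths to be significant at n = 36 gave mediation in about 6% of runs with no condition effect, 33% with an effect of 0.5 SD and 67% with 0.8 SD. These rates barely change with r. The second path almost always passes, so the verdict on mediation is the verdict on condition and subscale.

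**Extent.** Table 1 lists seven mechanism scores and four fidelity or outcome measures collected in both arms (WAI-SR overall, PPEM, CSACD-Satisfaction, service linkage). That makes 7 × 4 = 28 possible pairs, of which 3 share items.

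**The case against.** **The pairing is not spelled out.** The Analytic plan names no mediator–outcome pairs, and Table 1 labels the WAI-SR overall score as fidelity, keeping the narrower outcome label for satisfaction and linkage. On that reading the overall score might never be a mediation outcome, and an analysis plan not shown might list the pairs. This has some force, but Table 1 places the score under Outcomes, the WAI-SR section says the overall scale measures outcomes, and the mechanistic model runs from mechanisms to fidelity. The conflicting roles are assigned in the text; a later plan would have to override them.

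**A reader might infer that mediation will be reported whether or not anything happened.** The documents do not support that. Condition must still move the subscale, and that is a genuine test: with no effect, mediation appeared in only about 6% of runs.

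**A reader might also infer that any WAI-SR mediation will come out as 100%.** That holds only if all three subscales enter together, which no section says. With one subscale the direct effect need not be zero.

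**Same respondent, same sitting is not special to this pair.** True. The other survey measures share that feature, and so do the substitutes proposed below, apart from service linkage. What is special here is the shared items.

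**Mediation is secondary.** Also true: the Power analysis section calls these tests preliminary and limited in power, and Specific aim 3 describes a pilot that explores mechanisms. This lowers the severity but does not make an uninformative test informative.

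**Conclusion.** The concern holds for three pairs: Goal, Task or Bond as mediator with the WAI-SR overall score as outcome. For these, the mediator-to-outcome path is partly an identity (wholly so with all three subscales entered), and a finding of mediation adds nothing to the finding that condition moved the subscale.

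The overlap follows from the item counts and summed scoring alone, assuming complete, unweighted sums. The size of the one-subscale effect rests on equal subscale variances and an assumed r; r = 0 is the case that isolates the overlap. The significance rates come from single-level simulations, whereas the plan is multilevel, so they indicate size and are not exact for this trial.

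The main effect of condition on the WAI-SR overall score stands, as do the three subscales as mediators of other outcomes and every pair without shared items. This should be fixed before analysis, but it does not threaten the trial's main comparisons.

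**What to change.** Add to the Analytic plan, with a note under Table 1, that no WAI-SR subscale is paired with the WAI-SR overall score in a mediation model. Then:

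- test Goal, Task and Bond as mediators against PPEM (the other fidelity measure), CSACD-Satisfaction and service linkage;
- test the WAI-SR overall score as a mediation outcome only with CSACD-Collaboration, affect-based trust, psychological safety and card-sort agreement as mediators.

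The cost is one sentence and a table note. All these measures are already collected in both arms, so no data, visits or participants are added.

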### Data management

All collected data will use codes rather than subject names. Only the primary research team members will have access to participant identifiers. The research team will use a university-approved data entry, training, and management system that complies with the data security requirements of the Health Insurance Portability and Accountability Act of 1996 (HIPAA) [61] and the Health Information Technology for Economic and Clinical Health (HITECH) Act [62]. Aim 1 qualitative interview data will be de-identified and transcribed by study personnel or HIPAA compliant transcription services. Survey data for Aim 3 will be collected electronically at the end of the CFT meeting using secure online survey program software, with individual distribution links shared at the end of the CFT meeting. Web-survey data and qualitative transcripts kept by the research project will be coded with a unique identifying number for which the key will be separately stored and limited to primary research staff members who will only share these data to the extent necessary for required reporting purposes. Audio recording data from interviews and focus groups will be uploaded by study staff securely to the HIPAA compliant server.

### Analytic plan

Multilevel modeling with random intercepts and slopes will be used to examine differences in the targeted outcomes between CFT and CFT + AAR conditions, while accounting for the nested data structure. Specifically, this project will test the main effect of the AAR on implementation outcomes and child/family outcomes. Analyses will include the between-CFT meeting factor of condition (CFT vs. CFT + AAR) and within-CFT meeting factor of individual CFT member participant. The cross-level condition by participant interaction effect on the specified outcomes will be of primary interest.

A cross-level prediction model will test the extent to which the condition effect on the CFT outcomes is mediated by its proximal effect on team processes and emergent states. To assess the extent to which team processes are targeted by the AAR intervention, the Goal and Task subscales of the Working Alliance Inventory-Short Revised (WAI-SR) will be used to assess goal specification and strategy formulation, respectively [60, 63]. The Collaboration subscale of the Collaboration & Satisfaction About Care Decisions (CSACD) [57] measure will be used to assess the extent to which the AAR engages the team processes of communication and coordination. Several measures will be used to assess the extent to which emergent states are targeted by the AAR. Specifically, the Bond subscale of the WAI-SR and the McAllister Affect-Based Trust [58] measure will be used to assess trust. Edmondson’s Psychological Safety Climate [41] measure will assess the extent to which the AAR impacts the emergent state of psychological safety. To assess the extent to which the AAR engages the emergent state of shared mental models, a card-sorting task will assess CFT team shared mental models by examining perceptions of member roles, responsibilities, and goals across CFT team members. The concepts contained in the card sort will be representative of specific CFT roles, task responsibilities, and goals. To determine the feasibility, acceptability, and appropriateness of the AAR for CWS CFTs, those in the CFT + AAR condition will complete the Feasibility, Acceptability, and Appropriateness of Intervention Measures, respectively [51].

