## Mechanistic model and how AARs will improve child/parent outcomes

This project aims to leverage and apply knowledge from the field of team effectiveness research to improve CWS child/family outcomes. Specifically, the proposed project will enhance the current CFT services intervention with an evidence-based team development intervention (i.e., AARs) to improve the mechanisms of team processes and team emergent states for CFT members (including CWS caseworkers and children/families), resulting in enhanced service/clinical outcomes (i.e., specialty mental health services linkage).

The AAR team development intervention, hereafter referred to as CFT + AAR, is hypothesized to improve outcomes associated with the CFT meeting services intervention through enhanced team processes and emergent states. See Fig. 1 for the proposed mechanistic model and Table 1 for the proposed measures for model constructs. The AAR aims to boost emergent states of stronger shared mental models amongst team members (Cognition), and greater levels of trust and psychological safety amongst team members (Affect). Additionally, the AAR intends to improve team processes of communication and coordination (Actions) and positive perceptions of the specified goal and formulated strategy for the CWS child/family Action Plan (Transition). By enhancing the mechanisms of emergent states and team processes, the AAR facilitates improved fidelity and child/family outcomes. Specifically, CFT meeting fidelity is exemplified when child/family voice and shared decision-making amongst team members is present. When CFT meeting fidelity is enhanced, greater satisfaction with the child/family Action Plan may be achieved, ultimately resulting in successful specialty mental health services linkage.

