Immediately upon completion of each of the 5 CFT or CFT + AAR team meetings, the CWS caseworkers together with ~ 7 additional CFT members will provide data a via web-based online survey to assess mechanisms and outcomes. This results in 8 caseworkers leading 5 CFTs each for a total of 40 unique CFTs. Each of the 40 CFTs has ~8 participants, for a minimum total of 320 data points. See Fig. 2 for sampling.

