### Participants

There are four types of participants in this study. Participants will be (1) County CWS system leaders and caseworkers, (2) CFT informal and formal meeting members, (3) parents/caregivers with open CWS cases, and (4) children aged 6–17 with open CWS case. CWS caseworkers and CFT informal and formal support persons will be ≥ 18 years of age. Children and family members urrently open to CWS have a minimum age eligibility of 6 years to correspond with the CWS protocol for screening for behavioral health services need, and no maximum age limit for eligibility. Participants will be recruited from select regions, which will be determined in collaboration with CWS leadership prior to project implementation. Inclusion criteria for all groups of participants are intentionally broad to ensure valid analyses.

The research team will partner with County CWS to identify appropriate and representative CWS caseworkers to follow over the course of 5 CFT meetings. The 5 CFT meetings per CWS caseworker will be identified to best represent County CWS open cases. Additionally, only CFTs which include a child with an identified behavioral health services need will be included to optimize assessment of behavioral health services linkage. Behavioral health service need is determined by a preliminary administration of the Child & Adolescent Needs and Strengths (CANS) assessment by the CWS caseworker at the initial family visit. The CANS behavioral and emotional needs domain is employed for all children aged 6–17 as the screener for behavioral health services.

For children aged 6–17 open to CWS and with mental health services needs (identified via CANS screening and confirmed during initial CFT meeting perusual CWS), County Behavioral Health administrative data will be extracted to determine mental health service linkage. While children aged 6–17 may also participate in the CFT meeting, this is considered part of usual CWS services. No additional study participation from these children will be solicited. The proposed study will not apply any gender or minority exclusion criteria for participant selection. All efforts will be made to ensure that women and minority representation will be representative of County CWS.

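### Service linkage has one value per child, but the stated analysis treats team members as the within-CFT unit for all outcomes, so the interaction and the member-rated mediation path fail for linkage

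*Protocol article*

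**What the plan says.** The Analytic plan states one model family, with random intercepts and slopes, for the targeted outcomes, and says that it covers both implementation outcomes and child/family outcomes. Its factors are given as "Analyses will include the between-CFT meeting factor of condition (CFT vs. CFT + AAR) and within-CFT meeting factor of individual CFT member participant". The condition-by-participant interaction on the specified outcomes is named as the effect of primary interest. On mediation it says "A cross-level prediction model will test the extent to which the condition effect on the CFT outcomes is mediated by its proximal effect"; the mediators meant are the team processes and the emergent states. It describes no separate model for linkage and no averaging of ratings to CFT level.

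Linkage is among the outcomes so covered. Table 1 lists it as "CFT Clinical Intervention Outcome Behavioral Health Service Linkage". The section on the mechanistic model makes it the end of the causal chain: "resulting in enhanced service/clinical outcomes (i.e., specialty mental health services linkage". The Participants section gives its source: "County Behavioral Health administrative data will be extracted to determine mental health service linkage". The same section says of the children that "No additional study participation from these children will be solicited", so linkage is not a member rating.

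On numbers, Specific aim 3 has "8 caseworkers leading 5 CFTs each for a total of 40 unique CFTs", and the count of survey responses follows from the team size: "Each of the 40 CFTs has ~8 participants, for a minimum total of 320 data points". The Power analysis section sizes the CFT clinical intervention outcomes, the Table 1 label that also covers linkage, from these 320 member observations with a member-within-meeting correlation of 0.20.

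**The concern.** A member-level model needs an outcome that can differ between members of the same team. Linkage cannot: the child was linked or was not, and every member of that CFT carries the same value. The rating-scale mediators (WAI-SR Goal, Task and Bond, CSACD Collaboration, affect-based trust, psychological safety) do differ between members. The scientific question is whether teams with better processes and states link more children, which is a comparison between CFTs. A member-level slope within CFTs asks instead whether a member who rates higher than teammates has a better-linked child, and within one team that has no meaning.

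At stake is the last step of the mechanistic model, from team states to linkage, which is the clinical rationale for the AAR. Depending on where the random intercept is placed, the stated scheme either cannot detect that step or finds it too often when it is absent.

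**Working it through.** **Inputs.** From the article: 8 caseworkers, 5 CFTs each, so 40 CFTs (20 per arm); about 8 members per CFT, so 320 rows; ρ = 0.20; α = 0.05. Assumed, because the article does not give them: a 50% linkage rate, no caseworker effect, and two-sided tests.

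**1. The plan's own figure.** The Power analysis formula is n_eff = n/[1 + (n_clus − 1)ρ]. With n_clus = 40 (8 members × 5 meetings under one caseworker), 320/(1 + 39 × 0.20) = 320/8.8 = 36.4, which matches the stated 36. With n_clus = 8 (members within a meeting, as the text words it), 320/(1 + 7 × 0.20) = 320/2.4 = 133.3, which does not. So the calculation behind 36 clusters by caseworker while the text names the meeting, and the level of the random intercept cannot be taken as settled.

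**2. Linkage in the same formula.** Its correlation within a CFT is 1, not 0.20: 320/(1 + 7 × 1) = 40. There are 40 linkage values, whatever the number of rows.

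**3. Interaction.** Within each CFT, any contrast of linkage between members is exactly 0, in both arms. There is nothing from which to estimate a difference in such contrasts by condition.

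**4. Mediator slope with a CFT intercept.** The within-CFT slope is Σ(m_ij − m̄_j)y_j / Σ(m_ij − m̄_j)². Because y_j is constant in CFT j and the deviations sum to 0 there, the numerator is 0. In 4000 simulated trials the largest absolute value was 4e-17. When a strong true between-CFT association was simulated, a random-intercept fit (with slight noise added to linkage so that it would run) gave slopes of 0.0002 to 0.004, against about 0.55 for the regression on CFT means. With linkage copied unchanged to members, rejection was 0% in 1000 trials per setting, whatever the true effect.

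**5. Mediator path with no CFT intercept.** The approximate design effect is 1 + 7 × 0.20 × 1 = 2.4, whose square root is 1.55. The false-positive rate is then 2[1 − Φ(1.96/1.55)] ≈ 21%. Simulation under the null:

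| Analysis | Mediator-to-linkage path, rejection of a true null |
|---|---|
| 320 rows, no intercept | 22-26% across runs |
| 320 rows, caseworker intercept only | 22% and 25% in two runs |
| 40 records, CFT-mean rating | about 6% |

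**6. Condition effect on linkage.** With no random intercept at all, the design effect is 8 and 2[1 − Φ(1.96/2.83)] ≈ 49% (simulated 43-45%). With a caseworker intercept it is about 9%. With one record per CFT it was about 4%.

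**7. What CFT-level mediation could show.** With 40 records, the mediator-to-linkage path alone has power 44%, 71% and 86% for log-odds of 0.8, 1.2 and 1.6 per SD of team state. If condition moves team state by 0.5 to 0.8 SD and both paths must be significant, power falls to 10-21%, 16-35% and 19-42%. These effect sizes are assumptions.

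**The case against.** The best defence is that the faulty model is inferred. The Analytic plan does not name linkage; one reaches it through the terms for child/family and CFT outcomes, read with Table 1. The sentence on members fits the survey outcomes (WAI-SR overall, PPEM, CSACD satisfaction) well. A cross-level model does not exclude CFT-level mediators, and the article itself treats psychological safety as a group phenomenon and shared mental models as agreement across members. An article may leave the level and link function to the full analysis plan.

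Part of this stands. A reader might infer that the mediation test for linkage must be either zero or pseudo-replicated. The documents do not support that, since CFT-level mediators would avoid both faults and are not ruled out. But the article is not merely silent: it extends a member-level scheme and its interaction to child/family outcomes, and it counts clinical intervention outcomes as 320 member observations. For linkage that stated rule fails.

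Two other strong readings also go too far. A false-positive rate above 40% for condition on linkage needs a model with no random intercept, and the plan specifies random intercepts. The 44% to 86% in step 7 is power for one path, so it is not the mediation power lost.

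Finally, the article already calls the mediation tests preliminary and limited in power. That excuses low power, but not a path whose estimate is fixed in advance.

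**Conclusion.** The point holds for linkage only. As stated, the interaction of primary interest is not estimable for it, and with a CFT intercept its slope on the member-rated mediators is zero by construction. Both follow from algebra and need no assumption about the linkage rate. With an intercept only at caseworker level, the mediator-to-linkage path has a false-positive rate of about 22-26% against 5%. That figure rests on ICC 0.20, an assumed 50% linkage rate and no caseworker effect.

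The survey outcomes vary between members and are not affected. The card-sort agreement score is already team-level. Under a CFT intercept, the condition main effect on linkage is not distorted by copying the value to members. The plan should be changed, because linkage ends the mechanistic model and the remedy is cheap. The exposure is confined to analyses that the article already treats as preliminary, plus the interaction.

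**What to change.** In the Analytic plan:

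- Take linkage out of the member-level model. Analyse it with one record per child/CFT, linked yes or no on condition, and account for the randomised caseworker by a small-sample method suited to 8 caseworkers. This last part matters: with an assumed caseworker SD of 1 logit, simple regression on one record per CFT rejected a true null for condition 13% of the time.
- Exclude linkage from the condition-by-participant interaction.
- For mediation of linkage, use CFT-level mediators (the CFT mean of each rating scale and the card-sort agreement score), estimate both paths at CFT level, and report the result as exploratory.
- Keep the member-level model for the survey outcomes.

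The cost is a few lines and no new data. The downside is that the linkage analysis visibly rests on at most 40 records, with low mediation power. The number of linkage records should be stated at the same time, since the Power analysis and the Fig. 2 note speak of 8 child-family teams over 5 meetings, whereas Specific aim 3 has 40 separate CFTs.
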